### **Analysis Plan for Group 1 and Group 2**

- The treatment efficacy in the matched cohorts (i.e., Groups 1A and 2A) and in the cohort of patients receiving treating physician's choice of traditional systemic chemotherapy [i.e., no drug(s) available for target(s), no insurance coverage for recommended drug(s) = Group 1B and 2B, respectively] will be described.
- For the unresectable patients, determine whether the resectability rate in Group 1A is higher than in Group 1B.

### **Analysis Plan for Group 3:**

- For patients in 3A and 3B, the PFS of the last unmatched therapy (PFS1) and the PFS of the current therapy (PFS2) will be described. PFS1 will be collected retrospectively unless prospectively collected data is available. We will be limited in our ability to control for this. Thus, in order to avoid bias, we will have an independent physician assess the prior PFS. We will then estimate the percent of patients with  $PFS2/PFS1 > 1.5$ , and  $PFS2/PFS1 > 1.3$ .
- The treatment efficacy in the matched cohort (i.e., matched cohorts = 3A) and in the cohort of patients receiving treating physician's choice of traditional systemic chemotherapy [i.e., no drug(s) available for target(s), no insurance coverage for recommended drug(s) = Group 3B] will be described.

For PFS2/PFS1 ratio analyses, patients with matched therapy for PFS1 will be analyzed separately from patients with unmatched therapy for PFS1.

### **Analysis Plan for adverse events**

Treatment adverse events will be evaluated by the NCI Common Terminology Criteria for Adverse Events CTCAE version 4.03 (<http://ctep.cancer.gov/reporting/ctc.html>). Analyses will be performed for all patients enrolling to the study that subsequently receive matched therapy or physician's choice of traditional systemic chemotherapy. Frequency tabulation for all toxicities Grades 3-5 will be generated by the following:

- **Incidence.**
- **Patient.**
- **Disease.**
- **Drug.**
- **Drug combination (Note: given the infinite number of potential drugs and combinations, we cannot ascertain this *a priori*).**

### **Safety Stopping Rule**

Suspension of study enrollment will occur for ANY of the following overall (irrespective of patient group or treatment arm):

- a. Greater than 10 drug related SAEs.
- b. Greater than 10 drug related Grade 4-5 toxicities.
- c. Simon's two-stage design (Simon, 1989) will be used. The null hypothesis that the true response rate is 0.05 will be tested against a one-sided alternative. In the first stage, 13 patients will be accrued. If there are 0 responses in these 13 patients, the study will be stopped. Otherwise, 14 additional patients will be

accrued for a total of 27. The null hypothesis will be rejected if 4 or more responses are observed in 27 patients. This design yields a type I error rate of 0.0416 and power of 0.8011 when the true response rate is 0.20.  
(<http://www.csc.unc.edu/csc/aivanova/SimonsTwoStageDesign.aspx>)

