### **Patient Replacement**

Patients may be replaced if they have withdrawn from the study prior to having their tumor profiled in order to obtain 1150 evaluable patients with FoundationOne™ analyses.

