### **5.4.1 Adverse Event Monitoring**

Information about all adverse events, whether volunteered by the subject, discovered by investigator questioning, or detected through physical examination, laboratory test or other means, will be collected and followed as appropriate by the patient's treating physician.

This study will document all serious adverse events (as defined below in section 5.4.2 – Definitions) experienced by a subject while they are participating on the study and for 4 weeks after discontinuation of the matched and/or unmatched regimens chosen by their treating physician based on study navigation, or the start of a new therapy (whichever comes first).

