### **5.4.4 Expedited Reporting**

The Principal Investigator must be notified within 24 hours of learning of any serious adverse events, occurring during the study.

The UCSD Human Research Protections Program (HRPP) must be notified within 10 business days of “any unanticipated problems involving risk to subjects or others” (UPR).

Avera McKennan Cancer Institute Regulatory Department will be notified within 10 business days of “any unanticipated problems involving risk to subjects or others” and inform UCSD within the same time interval.

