## **6.2 Sample Size and Accrual**

This is a feasibility study with descriptive analysis as the primary analysis to characterize the study findings. We plan to enroll a total of 150 patients in Groups 1 and 2 and an unlimited number of patients in Group 3 (of up to 1000 patients) with their blood/tissues subject to the FoundationOne™ assay. We project to enroll patients in 30 months plus additional 6 months of follow-up. The total study period is 3 years. We expect that the accrual rate is 2 patients per month for Groups 1 and 2, and 4 patients per month for Group 3 in the first year. After the study mechanism is established and if we begin to see objective responses with matched therapy, we expect these rates to increase to 3 patients per months for Groups 1 and 2, and 5 patients per month for Group 3 in subsequent years. The total and percent of patients in Arm A and Arm B for each group will be determined to assess the feasibility of this study. With the comprehensive genomic profiling, we expect that 40% of the patients (N=30) will be in Arm A and 60% of the patients (N=45) will be in Arm B for all three patients groups.

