### **7.4 Data and Safety Monitoring**

The above referenced protocol has been audited since 2016 by the UCSD Moores Cancer Center Data Safety and Monitoring Board (DSMB). The study is not interventional in the traditional sense and as the title states is a navigational investigation. Since patients receive multiple different therapies or no therapies at all, it is not feasible to track safety results due the multiple modalities used. It has been decided that the DSMB will no longer audit this study, as of January 6, 2020.

I

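### The safety rule suspends enrolment at the 11th pooled drug-related event with no denominator against a target of 1150 patients, and Section 7.4 says safety results cannot feasibly be tracked

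*Protocol*

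**What the plan says.** The Safety Stopping Rule at the end of Protocol Section 6.6 begins "Suspension of study enrollment will occur for ANY of the following overall (irrespective of patient group or treatment arm". Item (a) is "Greater than 10 drug related SAEs" and item (b) is "Greater than 10 drug related Grade 4-5 toxicities". Neither item gives a rate, a number treated, a time window or operating characteristics. Item (c), a Simon two-stage rule on response, does give them.

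On size, the Study Summary lists 1150 subjects. Patient Replacement allows substitution "in order to obtain 1150 evaluable patients". Section 6.2 builds the total from two parts: "We plan to enroll a total of 150 patients in Groups 1 and 2", plus up to 1000 in Group 3.

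On monitoring, Section 7.4 says "it is not feasible to track safety results due the multiple modalities used" and ends the DSMB audit as of January 6, 2020. The same paragraph appears in Section 6.6, directly after the Simon output that follows the stopping rule. Elsewhere the collection duties remain. Section 5.4.1 states "This study will document all serious adverse events", and Section 5.4.4 states "The Principal Investigator must be notified within 24 hours of learning of any serious adverse events".

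**The concern.** There are two linked problems.

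First, an absolute count means different things at different sizes. It is a demanding limit in a large study and a loose one among the first few patients. Arm B receives traditional systemic chemotherapy and its events count equally, so some drug-related events are to be expected whatever the matched therapy does. If the count is likely to be reached at toxicity levels the investigators would accept, a suspension carries little information.

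Second, the rule needs a running, pooled, attributed tally, and the monitoring section says tracking safety results is not feasible. A site or IRB reading both cannot tell whether the rule is in force or who would notice that the count had been reached.

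**Working it through.** **The plan's own figures.** Only item (c) has stated operating characteristics. Take 13 patients in stage 1, stop at 0 responses, 27 in total, and reject at 4 or more responses. The exact two-stage binomial gives a type I error of 0.0416 at a response rate of 0.05, power of 0.8011 at 0.20, and an early-stopping probability of 0.95^13 = 0.5133. All three match the protocol. The size also adds up: 150 + 1000 = 1150. So the fault in (a) and (b) is not a miscalculation; they have no calculation behind them.

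**Inputs for (a) and (b).**
- Threshold: more than 10, so the 11th event triggers (Safety Stopping Rule).
- Target: 1150 (Study Summary; Patient Replacement; Section 6.2).
- Accrual in Section 6.2: 2 + 4 patients per month in year 1, then 3 + 5 per month, over 30 months. This gives 12 × 6 + 18 × 8 = 72 + 144 = 216, reading the rate for Groups 1 and 2 as combined. Reading it as per group gives 12 × 8 + 18 × 11 = 294.
- Number treated: not given. Assumed to be 50-70% of 1150, that is 575-805, with 1150 as the upper limit.
- Event rate: not given. Assumed range 1% to 10% of treated patients, with at most one event each.

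**What the 11th event represents.** 11/30 = 37%; 11/216 = 5.1%; 11/1150 = 0.96%. The rule treats these alike.

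**Probability that one item triggers.** P(X ≥ 11), with X binomial (n, p):

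| n treated | 1% | 2% | 3% | 5% | 10% |
|---|---|---|---|---|---|
| 216 | <0.001 | 0.005 | 0.06 | 0.52 | 0.997 |
| 294 | <0.001 | 0.04 | 0.27 | 0.87 | >0.999 |
| 575 | 0.03 | 0.60 | 0.96 | >0.999 | >0.999 |
| 805 | 0.19 | 0.93 | 0.999 | >0.999 | >0.999 |
| 1150 | 0.60 | 0.998 | >0.999 | >0.999 | >0.999 |

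The expected number of patients to the 11th event is 11/p: 220 at 5% and 110 at 10%. Several events in one patient, or either of two items being enough, would raise these probabilities.

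**Early behaviour.** At a true rate of 50%, again with one event per patient, the rule has fired with probability 0.06 by patient 15, 0.41 by patient 20, 0.79 by patient 25 and 0.95 by patient 30. It cannot fire within the first 10 patients unless someone has more than one event.

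**Monitoring passages side by side.** The stopping rule makes suspension mandatory on a count. Section 7.4, and its copy after the rule, say safety results cannot feasibly be tracked. Sections 5.4.1 and 5.4.4 still produce SAE reports, and SAE incidence is still listed as an endpoint. No passage withdraws the rule or assigns the count to another role.

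**The case against.** Several points on the other side carry weight.

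- **Rates and size are assumed.** The protocol states no event rate. If accrual ends near 216 with only 50-70% treated (108-151 patients), the trigger probability at 5% is 0.02-0.14. This stands: near-certain triggering is a statement about large enrolment. But 1150 is the stated target, and a count without a denominator is not calibrated at either size.
- **The rule does respond to extreme early toxicity.** A reader might infer that it misses a very high early rate altogether. It does not: at 50% it has very probably fired by patient 30, and sooner if patients have several events each.
- **The action is limited and other safeguards exist.** The consequence is suspension of enrolment, not termination of the study. Prompt SAE notification, reporting of unanticipated problems within 10 business days and annual reporting of other events remain. It would be wrong to say that patients are left unprotected. The rule does not, however, describe a review or a route to resumption.
- **Grade 4 data are planned.** Section 5.4.1 alone might suggest that only serious events are recorded, leaving item (b) without data. The document does not support that. The dose-modification section tabulates toxicities of Grade 3 and above for approved drugs, and Sections 6.4 and 6.6 plan documentation and tabulation of Grades 3-5.
- **Ending the DSMB audit does not repeal the rule.** The Principal Investigator still receives each SAE and could count them. That the rule is not being run is an inference the text does not establish. What the text does establish is that its status and owner are unclear.

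**Conclusion.** The point holds. Items (a) and (b) fix a pooled count of 11 events with no denominator in a study planned for up to 1150 patients. With 575 or more treated, and at most one event per patient, suspension has a probability of at least 0.60 at a 2% event rate and at least 0.96 at 3%. At about 216 treated it is 0.52 at 5% and 0.997 at 10%. These figures rest on assumed rates and an assumed number treated. The lack of a denominator, and the conflict between the stopping rule and Section 7.4, rest on the text alone. Both are fixed in the protocol, so a separate analysis plan would not remove them. This should be corrected, because a mandatory trigger is both uncalibrated and set against the protocol's own monitoring statement.

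**What to change.** 1. Restate (a) and (b) as a limit on the proportion of treated patients with at least one qualifying event, tabulated by number treated. An exact binomial or beta-binomial limit would serve; the form matters less than having a denominator. The investigators should choose the tolerable rate and state the resulting trigger probabilities, as item (c) already does for response.
2. Base the count for (a) on the SAE reports already required under Sections 5.4.1 and 5.4.4. Item (b) can use the Grade 3-5 tabulation already planned.
3. Reconcile the Safety Stopping Rule with Section 7.4 and its copy in Section 6.6: state whether the rule is in force and which role keeps the count now that the DSMB audit has ended.

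The cost is amendment wording and a short boundary table. No new data collection is needed.

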#### **Exploratory Endpoints**

Estimate the:

1. Overall response rate (ORR) defined as partial (PR) or complete response (CR) occurring at any point during treatment according to Response Criteria in Solid Tumors (RECIST) 1.1 in all treatment groups
2. Regression rate as a percent defined by best percent size reduction in target lesions from baseline to discontinuation in all groups
3. Progression free survival (PFS) defined as time from first dose to disease progression or death, whichever occurs first
4. Overall survival (OS) defined as time from first dose to death due to any cause
5. Resection rate as a percent of patients previously considered unresectable that are able to be resected in all groups
6. Change in biochemical tumor markers of disease as defined as the best percent change from baseline in relevant tumor markers from first dose to discontinuation
7. Incidence of serious adverse events in all groups according to CTCAE v4.03

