### **Feasibility**

This feasibility study is an evaluation and analysis of the potential of a proposed methodology that is based upon molecular profiling to support decision making in individualized cancer therapy for patients with incurable malignancies. Like other feasibility studies, we will objectively and rationally uncover the strengths and weaknesses of this approach in the academic environment of UCSD with our collaborators. This feasibility study will evaluate this methodology's potential for success. We termed this a feasibility study because genomically driven trials, especially in this setting, are relatively new. As such, we might encounter logistical hurdles that will need to be addressed and overcome before a definitive trial is performed.

For the primary objective, we consider matching therapy for  $\geq 40\%$  of patients ( $N \geq 30$ ) in each Group to define a successful feasibility endpoint. Additional measure of feasibility will be the ability to enroll patients in each Group, the turnaround time for genomic analysis, and the ability to identify actionable genomic alterations.

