### **6.6 Exploratory Analyses**

Exploratory analyses will be conducted to evaluate efficacy and adverse event outcomes in each group and ARM and for comparison across groups.

All exploratory analysis will test the hypothesis of greater response rate in Arm A than that in Arm B. With an estimated sample size of 30 (ARM A) and 45 (ARM B) in each group, we can estimate the response rate with a standard error no larger than 0.09 and 0.07, respectively. We will have sufficient statistical power to detect the difference between groups only if the difference between groups is sufficiently large. For example, with the sample size of 30 and 45 for Arm A and Arm B, we will have 79% power to detect the response rate of 0.25 and 0.05 between the two arms with one-sided 10% type I error rate using the continuity corrected chi-square test.

We will have more than 80% power to detect the difference between Arm A and Arm B using the log-rank test when the median PFS is 4 months and 2 months for the two arms, respectively.

In addition, in Group 1A, we will estimate the proportion of patients who are initially unresectable but converted to resectable after 8 weeks of the matched treatment, or if ever resected. With 30 patients, we expect to see at least one patient becomes resectable with a probability of 0.79, 0.96, and 0.99 if the conversion rate is 0.05, 0.10, and 0.15, respectively. We expect to see at least 2 patients become resectable with a probability of 0.82 and 0.95 if the conversion rate is 0.10 and 0.15, respectively. One-sided nominal level at 10% will be used to declare statistical significance. No P value adjustment for multiplicity will be applied due to the exploratory nature of the study. All study results need to be confirmed by future studies with larger sample sizes.

- The response rate (proportion of patients reaches CR or PR) will be estimated based on RECIST for each patient group and each treatment arm.
- The tumor regression rate (in %) will be calculated by the percent tumor size reduction from baseline to after treatment will be determined in and across patient groups.
- Progression-free survival (PFS) and overall survival (OS) will be determined in and across patient groups and treatment arms.

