### Simon's Two-Stage design

This program generates Simon's optimal two-stage designs (Simon, 1989) and admissible designs from Jung et al. (2004) for Phase II single arm clinical trials.

1. Simon R (1989). *Controlled Clinical Trials* 10: 1-10. [Click here to download Simon's \(1989\) article.](#)

Type I error rate,  $\alpha$  (one-sided):

Power:

Response probability of poor drug,  $p_0$ :

Response probability of good drug,  $p_1$ :

| $n$ | $n_1$ | $r_1$ | $r_2$ | Type 1 Error | Power  | $EN_0$ | Probability of early stopping | Interval for $w$ | Comment |
|-----|-------|-------|-------|--------------|--------|--------|-------------------------------|------------------|---------|
| 27  | 13    | 0     | 3     | 0.0416       | 0.8011 | 19.8   | 0.5133                        | [0.5973,1]       | Minimax |

$n$  is the total number of subjects

$n_1$  is the number of subjects accrued during stage 1

$r_1$ , if  $r_1$  or fewer responses are observed during stage 1, the trial is stopped early for futility

$r_2$ , if  $r_2$  or fewer responses are observed by the end of stage two, then no further investigation of the drug is warranted

$EN_0$  is the expected sample size for the trial when response rate is  $p_0$

Interval for  $w$  is the set of values  $w$  such that the design minimizes  $w * n + (1 - w) * EN_0$

The above referenced protocol has been audited since 2016 by the UCSD Moores Cancer Center Data Safety and Monitoring Board (DSMB). The study is not interventional in the traditional sense and as the title states is a navigational investigation. Since patients receive multiple different therapies or no therapies at all, it is not feasible to track safety results due the multiple modalities used. It has been decided that the DSMB will no longer audit this study, as of January 6, 2020.

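### The two-stage response rule in the Safety Stopping Rule is not limited to matched-therapy patients, so its stated error rates do not describe matched therapy; it also names two different consequences

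*Protocol*

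**What the plan says.** The Safety Stopping Rule in Protocol section 6.6 opens with "Suspension of study enrollment will occur for ANY of the following overall (irrespective of patient group or treatment arm" and then lists three triggers. Items (a) and (b) count drug-related serious adverse events and Grade 4-5 toxicities. Item (c) counts tumour responses against a null response rate of 0.05. Stage 1 has 13 patients: "If there are 0 responses in these 13 patients, the study will be stopped". Otherwise 14 more are added, and the null is rejected with 4 or more responses in 27. The operating characteristics follow: "This design yields a type I error rate of 0.0416 and power of 0.8011 when the true response rate is 0.20".

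The software output reproduced under Simon's Two-Stage design describes a tool for single-arm phase II trials. Its legend for the first boundary says that if that number or fewer "responses are observed during stage 1, the trial is stopped early for futility".

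On the arms, section 6.2 expects that "40% of the patients (N=30) will be in Arm A and 60% of the patients (N=45) will be in Arm B". Arm B receives chemotherapy chosen by the treating physician. For response, sections 6.4 and 6.6 use planning rates of 0.25 and 0.05: "we will have 79% power to detect the response rate of 0.25 and 0.05 between the two arms".

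**The concern.** A Simon design tests one response rate in one cohort. Its error rates answer a question about matched therapy only if the patients counted received matched therapy. The only statement of scope over item (c) includes both arms, and item (c) does not narrow it. Someone applying the rule as written would count the first 13 treated patients from either arm, most of them expected to be on chemotherapy.

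Two errors then become possible. Non-response in Arm B can trigger the boundary although matched therapy works. Conversely, responses in Arm B could carry an inactive matched strategy past it.

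Separately, the lead-in makes the consequence a suspension of enrolment, while item (c) makes it a stop of the study. These are different actions, and the text does not say which governs.

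**Working it through.** **Inputs**
- Design, from item (c): n1 = 13, stop at 0 responses; n = 27, reject at 4 or more; null rate 0.05, alternative 0.20.
- Arm mix, from section 6.2: 40% Arm A, 60% Arm B.
- Planning response rates, from sections 6.4 and 6.6: Arm A 0.25, Arm B 0.05.

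**Formulas**
- Stage 1 stop: P(0/13) = (1 − p)^13.
- Passing both stages: sum over x = 1 to 13 of P(X1 = x) × P(X2 ≥ 4 − x), with X1 ~ Bin(13, p) and X2 ~ Bin(14, p).
- Pooled rate when both arms count: p = 0.4 × pA + 0.6 × pB.

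**Step 1: the plan's own figures.** At p = 0.05, P(0/13) = 0.95^13 = 0.5133 and P(pass) = 0.0416. At p = 0.20, P(pass) = 0.8011. The stated figures reproduce exactly, so the arithmetic of the design is sound for a single cohort.

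**Step 2: the rule as worded, against Arm A only**

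| Arm A rate | Arm B rate | Pooled p | P(0/13), pooled | P(0/13), Arm A only | P(pass), pooled | P(pass), Arm A only |
|---|---|---|---|---|---|---|
| 0.25 | 0.05 | 0.4×0.25 + 0.6×0.05 = 0.13 | 0.87^13 = 0.164 | 0.75^13 = 0.024 | 0.457 | 0.922 |
| 0.20 | 0.05 | 0.4×0.20 + 0.6×0.05 = 0.11 | 0.89^13 = 0.220 | 0.80^13 = 0.055 | 0.332 | 0.801 |

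Fixing the first 13 patients at 5 Arm A and 8 Arm B, instead of letting the split vary, changes little: 0.75^5 × 0.95^8 = 0.157 in the first row.

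**Step 3: masking, under assumed Arm B rates.** The Protocol gives no planning rate for Arm B above 0.05, so these are illustrations. Arm A is set at the null, 0.05. Counted alone, it passes stage 1 with probability 1 − 0.513 = 0.487 and passes both stages with probability 0.042.
- Arm B at 0.10: pooled p = 0.08; passing stage 1 = 0.662; passing both stages = 0.159.
- Arm B at 0.20: pooled p = 0.14; passing stage 1 = 0.859; passing both stages = 0.518.

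**Step 4: timing if only Arm A counts.** The matched share of enrolled patients is 40% (section 6.2). The molecular matching text in section 3.2 implies a lower share: 40% of the 50-70% with actionable alterations, or 20-28%. Thirteen matched patients then need 13/0.40 = 33 to 13/0.20 = 65 enrolled.

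**The case against.** The strongest reply is that Arm A was plainly meant. The software text is for single-arm trials, and the lead-in's scope phrase fits the toxicity counts in (a) and (b) better than a response test. On that reading a wrong stop is unlikely (2.4% at a response rate of 0.25). The intent is plausible, but the only scope the Protocol states is the opposite, and a stopping rule has to be executable as written.

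It can also be said that the two consequences reconcile, because (c) is a sub-item of a sentence about suspending enrolment. That is a fair reading and supports keeping the lead-in's wording, but item (c) still says something else.

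Third, the practical effect may be small. The Protocol says the study was audited from 2016 and that this auditing ended in January 2020. At planned accrual (6 a month in year one, then 8) and the lowest matched share, 27 Arm A patients need 27/0.20 = 135 enrolled: 72 in the first year, then 63/8 = about 8 months, so about 20 months. Both looks may well have passed; actual accrual is not given. This stands, and it limits the severity.

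A reader might also infer that the rule is illegitimate because it sits under a safety heading and acts on an exploratory endpoint (section 1.5: "Overall response rate (ORR) defined as partial (PR) or complete response (CR) occurring at any point during treatment"). The documents do not support that. Halting when nobody responds is a reasonable protection, particularly for treatment-naive patients who take matched drugs before chemotherapy. The heading is a labelling matter, and the rank of the endpoint does not bar a futility rule.

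**Conclusion.** The point holds for the scope and consequence of item (c). As worded, the rule pools the arms, and the stated 0.0416 and 0.8011 then do not describe matched therapy. With the Protocol's planning rates and mix, the chance of a stage 1 stop rises from 2.4% to 16%, and the chance of passing both stages falls from 92% to 46%. At the design alternative for Arm A with Arm B at 0.05, power falls from 80% to 33%. These figures assume that counted patients follow the 40:60 mix and respond independently.

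A reader might go further and infer that chemotherapy responses are likely to hide an inactive matched strategy. The documents do not support that: masking requires Arm B to respond above 0.05, the only planning rate the Protocol gives for that arm. It is possible, but its size rests on assumption. Nor do the documents show that both arms were in fact counted.

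Severity is low to moderate. If Arm A was always the population applied, or both looks are past, what remains is a text correction and a reporting duty.

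**What to change.** In item (c), define the 13 and 27 patients as response-evaluable Arm A patients, state that the lead-in's phrase on treatment arm does not apply to (c), and label (c) a futility rule. Give one consequence, the lead-in's suspension of enrolment, in place of stopping the study. This keeps an automatic action. If the looks have already taken place, report which patients were counted at each.

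The change needs no new patients, visits or data. Its cost is a later first look: about 33 to 65 enrolled patients are needed to reach 13 matched ones, against as few as 13 if both arms count. More patients may therefore start matched therapy before an inactive strategy is noticed.
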